##### Tardieu Scale

Spasticity is assessed using the Tardieu Scale [28]. This scale is of better metrological quality than the Ashworth scale usually used in this type of study [29]. It allows the analysis of the resistance to stretching at several different speeds. Two speeds are used: XV1 is the slowest possible stretching speed and XV3 is the fastest possible stretching speed. Two results are noted: first, the Tardieu angle, which is the difference between the angle of passive joint amplitude obtained at XV1 and the angle of the first resistance to stretching at XV3, and second, the Tardieu intensity score of the resistance to stretching measured by an ordinal score from 0 to 4.

The end point was the progression from the allocation to 1 month later (V0 to V1) and from the allocation to 3 months later (V0 to V2), focusing on muscle groups such as the triceps surae (knee flexed and extended), carpal flexors, and elbow flexors. This score can be applied to muscles that have not been injected, but given the global action of baclofen, measurement of all these muscle groups was essential.

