##### Modified Ashworth Scale

The MAS evaluates muscle tone of the same muscles evaluated with the Tardieu Scale. However, it primarily assesses the intensity of resistance to stretching without considering stretching speed [30]. It is therefore much less precise than the Tardieu Scale in terms of the increase in the myotatic reflex, but it allows a very global consideration of the modifications of the intrinsic biomechanical properties of the muscle fibers and the dystonia of the muscles examined. The end point was the progression from the allocation to 1 month later (V0 to V1) and from the allocation to 3 months later (V0 to V2) on the same muscle groups.

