### Statistical Methods

#### Statistical Methods for Primary and Secondary Outcomes

The baseline characteristics of the participants are described for the 3 treatment groups and the pairwise standardized differences are used to compare the distribution of baseline covariates between treatment groups.

The variation in the Fugl-Meyer score between the “toxin” and “baclofen” groups is compared using linear regression models. First, the model contains the treatment group as the explanatory variable and the Fugl-Meyer delta score as the response variable. The adjusted model then incorporates the patient’s age, the center, and any associated treatment as explanatory variables, in addition to treatment. The associated treatment is represented by a binary variable indicating the use of at least 1 serotonin reuptake-inhibiting antidepressant (yes or no) or at least 1 benzodiazepine (yes or no). This list is validated during the descriptive analysis of concomitant treatment.

The primary objective tests the superiority of the “toxin” versus “baclofen” in motor recovery at 3 months using 2-sided tests at a 5% α level. The secondary objective aims to demonstrate the clinical equivalence of the “toxin” versus the “placebo” in motor recovery after 3 months, using a 1-sided noninferiority test at a 5% α level and a margin of 13 FMA points to assess noninferiority.

To assess the efficacy of these treatments on spastic symptoms (MAS, Tardieu angle, and Tardieu Scale), 2-tailed *t* tests at a significance level of 5% are conducted for pairwise comparisons. The first analysis is carried out on all muscle groups, and a second analysis is carried out on the muscle groups that have been injected.

For the FMA at 1 month and the variation score between allocation and the second postallocation visit which consists of the RMA the Barthel Index, the Rankin score, the reaction time, satisfaction, pain, and the RNLI, the analyses will be descriptive using the usual statistical measures in each group with a 95% CI.

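### Spasticity is tested with up to 36 unadjusted pairwise t tests at 5%, with no key comparison and no correction, so the family of tests is not held at 5%

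*Protocol article*

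**What the plan says.** Under Statistical Methods for Primary and Secondary Outcomes, the article names three measures of "spastic symptoms (MAS, Tardieu angle, and Tardieu Scale" and states that two-tailed t "tests at a significance level of 5% are conducted for pairwise comparisons". It adds: "The first analysis is carried out on all muscle groups, and a second analysis is carried out on the muscle groups that have been injected".

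The Tardieu Scale section sets two change periods: "The end point was the progression from the allocation to 1 month later (V0 to V1) and from the allocation to 3 months later". The Modified Ashworth Scale section sets the same two periods, the second running "from the allocation to 3 months later (V0 to V2) on the same muscle groups". Several muscles are measured in each patient, "focusing on muscle groups such as the triceps surae (knee flexed and extended), carpal flexors, and elbow flexors". Because baclofen acts on the whole body, "measurement of all these muscle groups was essential", injected or not.

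Reducing spasticity is listed under Secondary Objectives, not Exploratory Objectives. In the same statistical section the 1-month FMA, RMA, Barthel, Rankin, reaction time, satisfaction, pain and RNLI are only described, with 95% CIs. The article therefore separates outcomes that are tested from outcomes that are described, and spasticity is among those tested.

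**The concern.** A per-test level of 5% with many tests and no named key test lets any one significant contrast be read as a finding. The abstract's conclusion promises recommendations on the primary treatment of early spasticity, so a significant spasticity contrast would carry weight.

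Two further matters are left open or given up. The article does not say how several muscles in one patient become one observation in a t test. The t tests on change scores also make no use of the V0 score or center as covariates, although randomization is stratified by center (Allocation) and the adjusted FMA model includes center.

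**Working it through.** The 5% is a chosen setting and no family-wise figure is stated, so there is no figure of the plan's own to reproduce.

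**Inputs from the article.** Three measures; two change periods (V0–V1, V0–V2); two muscle sets (all, injected); three arms, hence three pairs. The pairs and periods are not listed beside the t tests. They follow from the word pairwise, the three arms and the endpoint sections. 179 patients were randomized 2:2:1.

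**Inputs assumed.** A split of 72/72/35; four measurements per patient (triceps surae with knee flexed and with knee extended, carpal flexors, elbow flexors), although the article gives that list as examples; and all correlations.

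**Number of tests, one score per patient.** 3 measures × 2 periods × 3 pairs = 18 per muscle set; 18 × 2 = 36 for both sets. For toxin versus baclofen alone, 3 × 2 = 6 per set.

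**Chance of at least one false positive if no arm differs and the tests were independent.** 1 − 0.95^k:
- k = 6: 26.5%
- k = 18: 60.3%
- k = 36: 84.2%

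The tests are not independent, so these figures are too high. A null simulation (2,500 runs, normal data, patient mean over four measurements, one muscle set) gave:

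| Assumed correlation between scales / visits / muscles | 18 tests, all pairs | 6 tests, toxin v baclofen |
|---|---|---|
| 0.3 / 0.5 / 0.3 | 50.1% | 24.1% |
| 0.5 / 0.5 / 0.3 | 47.8% | 23.3% |
| 0.7 / 0.7 / 0.5 | 37.6% | 17.6% |
| 0.8 / 0.8 / 0.7 | 32.9% | 14.4% |
| 0.9 / 0.9 / 0.9 | 26.8% | 12.0% |

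The simulation error is at most about √(0.25/2500) = 1 percentage point. The full 36 tests were not simulated. Adding the second muscle set can only raise these rates.

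**If muscles were entered as separate observations.** The design effect is DE = 1 + (m − 1)ρ, and the true error of a nominal 5% test is 2 × [1 − Φ(1.96/√DE)]. With m = 4:
- ρ = 0.3: DE = 1.9, error 15.5%
- ρ = 0.5: DE = 2.5, error 21.5%

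The inflation falls with fewer muscles. At m = 2 the same correlations give 8.6% and 11.0%, which matters for the injected-muscle analysis.

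**The case against.** The strongest reply is that an article condenses a fuller plan. How muscles are combined, and whether these tests are labelled exploratory, may be settled in a document not shown. This stands for the unit of analysis. It does not fully answer the multiplicity point, because the article itself fixes the test, the 5% level, the pairwise scope and the two muscle sets, and treats most other secondary outcomes descriptively.

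A reader might infer more than the documents support:

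- **Every spasticity test exceeds 5%.** Not shown. One summary score per patient fits the text, and each single pre-named test then keeps 5%.
- **There are 144 tests.** This needs each of the four measurements tested separately in both sets (36 × 4). The article does not say so.
- **Baseline is ignored, or leaving out center inflates error.** Both endpoints are changes from V0, so baseline is already subtracted. Omitting V0 and center as covariates costs precision. It does not raise the error rate, and after stratification by center an unadjusted test tends to be conservative.
- **All three measures are ordinal.** The article does define "the Tardieu intensity score of the resistance to stretching measured by an ordinal score from 0 to 4", but the Tardieu angle is a difference between two angles.
- **Spasticity is the only secondary family tested besides noninferiority.** The section on additional analyses also compares toxin with baclofen by regression on FMA-UE and FMA-LE in two subgroups.

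It is also fair that no difference between any arms is an unlikely truth when the article calls both drugs established spasticity treatments. That weakens the 18-test figure for the placebo pairs. It has less force for toxin versus baclofen, where six tests still give 12% to 24%.

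**Conclusion.** The point holds as one of multiplicity and analysis choice in a secondary objective. Up to 36 tests at 5%, with no key comparison or correction, do not hold the family at 5%. Even with one score per patient, the chance of at least one false positive is about 27% to 50% for 18 tests. This rests on the assumed correlations, the 72/72/35 split and no true difference.

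The 15% to 21% error per single test is conditional. It applies only if a patient's muscles are treated as independent observations, and it rests on four measurements per patient and a correlation of 0.3 to 0.5, neither of which the article fixes. The missing adjustment for V0 score and center is a loss of precision only. The primary FMA comparison of toxin with baclofen is not affected.

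**What to change.** - State the unit of analysis. For each scale, use either the patient mean over muscle groups, or a mixed model with a patient random effect and muscle group. Adjust for the V0 score and center in both cases.
- Name one key spasticity comparison: toxin versus baclofen, V0 to V2, on one muscle set that the sponsor chooses before unblinding. The Tardieu Scale section gives a reason for choosing all muscle groups.
- Apply Holm over the three scales: the smallest p value against 0.05/3 = 0.0167, the next against 0.025, the last against 0.05.
- Report V0 to V1, the other muscle set and the comparisons with placebo as estimated differences with 95% CIs and no significance claims, in line with the descriptive reporting already planned for most other secondary outcomes.

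The cost is a change of wording and a standard model on data already collected. The downside is fewer formal tests. In December 2024 the article reports that no analysis had been run and the blind was in place. A change made before unblinding would therefore not be driven by the results.

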**Objective:**

This study aims to compare the motor recovery effects of botulinum toxin versus oral baclofen. The hypothesis is that botulinum toxin is more supportive of motor recovery than baclofen and enhances functional recovery.

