**Methods:**

The study is a multicenter, controlled phase IV, comparative, prospective, randomized, double-blind, double-dummy, superiority trial to compare the toxin and baclofen, and a noninferiority trial to compare the toxin and the placebo. It focuses on the time course of the Fugl-Meyer Motor Assessment (FMA) as the primary outcome. The main inclusion criterion is patients with a single stroke in the past 2 months. Treatment comprises 1 intramuscular injection at treatment initiation and oral tablets for 4 months. Randomized patients are allocated to 3 arms: botulinum toxin with placebo baclofen, baclofen with placebo botulinum toxin, and placebo baclofen with placebo botulinum toxin. FMA scores are assessed at pretreatment, 1 month, and 3 months later. Spasticity, functional abilities, activities of daily living, pain, and quality of life are also evaluated. Adverse effects are monitored. A positive difference of 13 points in the FMA time course between the botulinum toxin and baclofen groups is considered a relevant effect. The data analysis plan involves linear regression models to compare primary and secondary outcomes, with adjustments for covariates such as age, center, and associated treatments. Subgroup analyses will examine proportional recovery profiles, and missing data in Fugl-Meyer scores will be addressed using imputation methods.

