#### Secondary Objectives

Our secondary objectives are as follows:

To compare the effects of botulinum toxin A and placebo on motor recovery (FMA) over 3 months and establish clinical equivalence.To evaluate the impact of treatment on motor recovery (main objective and placebo comparison) based on initial FMA-upper extremity (FMA-UE) scores.To assess changes in motor recovery (FMA) during the first month of treatment.To compare the effectiveness of the treatments in reducing spasticity symptoms over 1 and 3 months using the Tardieu Scale and Modified Ashworth Scale (MAS).To evaluate functional improvement 3 months after treatment using the Rivermead Motor Assessment (RMA), Rankin score, and Barthel score.

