#### Exploratory Objectives

To assess the impact of treatments on pain using a visual analog scale (VAS) at 1 and 3 months.To evaluate the quality of life over 3 months using the Reintegration to Normal Life Index (RNLI), a scale validated for patients with vascular hemiplegia.To compare reaction times at baseline, 1 month, and 3 months to investigate cognitive effects of treatment.To measure patient satisfaction with treatment at 1 and 3 months.

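### Eight non-primary outcomes get per-arm summaries only; no between-arm estimate is planned, which conflicts with the abstract and does not match several stated aims

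*Protocol article*

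**What the plan says.** In the protocol article, Statistical Methods for Primary and Secondary Outcomes covers three kinds of analysis.

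- The 3-month FMA change is compared between toxin and baclofen by unadjusted and adjusted linear regression. Toxin is compared with placebo by a noninferiority test.
- The spasticity measures are compared pairwise between arms by t tests.
- For the 1-month FMA, and for the change from V0 to V2 in the Rivermead, Barthel and Rankin scores, reaction time, satisfaction, pain and the RNLI, "the analyses will be descriptive using the usual statistical measures in each group with a 95% CI".

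Other sections describe these outcomes differently. Under Methods, the abstract states: "The data analysis plan involves linear regression models to compare primary and secondary outcomes". Its Objective gives the hypothesis that "botulinum toxin is more supportive of motor recovery than baclofen and enhances functional recovery". The exploratory objectives include "To compare reaction times at baseline, 1 month, and 3 months to investigate cognitive effects of treatment" and "To assess the impact of treatments on pain using a visual analog scale (VAS) at 1 and 3 months". The section on treatment satisfaction says that satisfaction was compared at V1 and V2.

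**The concern.** A treatment effect is a contrast between arms. In the subacute phase after stroke every arm is expected to improve, so the mean change within one arm mixes spontaneous recovery, rehabilitation and treatment. The article makes this point itself: Strengths and Limitations calls the placebo arm crucial for separating treatment effects from natural recovery. Per-arm summaries do not use that arm as a control.

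At stake is whether the trial will report any estimate of the effect on function, pain, reaction time, quality of life and satisfaction. If contrasts are not fixed beforehand, those that appear in the results may be chosen after the data are seen.

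**Working it through.** The protocol states no figure on this point, so the check is mainly a comparison of sections.

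**Step 1: is the per-group wording deliberate?** The same section specifies between-arm methods for the 3-month FMA and for spasticity, then changes to summaries in each group for the remaining outcomes. It reads as a choice made for those outcomes, not as a detail left open.

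**Step 2: aims against the planned analysis.** All eight outcomes stand under the article's Secondary outcomes heading, so the abstract's sentence on regression covers them on its face.

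| Outcome | Wording of the aim | Planned analysis |
|---|---|---|
| 1-month FMA | "To assess changes in motor recovery (FMA) during the first month of treatment" | per-arm summary |
| Rivermead, Rankin, Barthel | "To evaluate functional improvement 3 months after treatment using the Rivermead Motor Assessment (RMA), Rankin score, and Barthel score"; the abstract's hypothesis adds enhanced functional recovery | per-arm summary |
| Reaction time | compared, to investigate effects of treatment | per-arm summary |
| Pain | impact of treatments | per-arm summary |
| Satisfaction | compared at V1 and V2 | per-arm summary |
| RNLI | evaluated over 3 months | per-arm summary |

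The aims for reaction time, pain and satisfaction point to a contrast between arms. For function, the contrast comes from the abstract's hypothesis. For the 1-month FMA and the RNLI, it comes only from the abstract's sentence on regression.

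**Step 3: where regression is actually planned.** It is planned for the 3-month FMA change and, in the section on additional analyses, for FMA-UE and FMA-LE within the recoverer and nonrecoverer groups. None of the eight outcomes is among these.

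**Step 4: what per-arm results would still allow.** Suppose the mean change is r + t in a treated arm and r under placebo, where r is recovery common to the arms. Neither mean isolates t, but their difference does: (r + t) − r = t. If the per-arm 95% CIs have half-widths h1 and h2, the unadjusted difference has a 95% CI of half-width about √(h1² + h2²). For equal arms, h1 = h2 = h, this is √2 × h, or about 1.41h. An unadjusted contrast can therefore be recovered from published means and intervals. An adjusted one cannot, and for the ordinal Rankin score the route depends on which summaries are reported.

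**Step 5: visits.** The sections on pain and on reaction time define change from V0 to V1 and from V0 to V2. The statistical sentence gives only V0 to V2. Satisfaction is assessed at V1 and V2, so a change from V0 cannot be formed.

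**The case against.** Descriptive reporting of secondary and exploratory outcomes is an accepted choice. It is prudent here, with several such outcomes and 179 patients randomized against a revised target of 214. Pain, the RNLI, reaction time and satisfaction are listed as exploratory objectives. The secondary objectives for the 1-month FMA and for function use verbs that fit a descriptive report, and the reaction-time objective can be read as a comparison over time. The functional part of the hypothesis appears only in the abstract; the hypothesis in the Introduction and the main objective concern motor recovery. The abstract's sentence on regression may be shorthand, since regression does cover some secondary outcomes, namely the FMA subscores within subgroups. Finally, an SAP that is not shown could add between-arm differences.

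Much of this stands. Nothing requires significance tests, and the objectives for the 1-month FMA and function do not by themselves promise a comparison. What remains is that the article states a within-arm method for these outcomes while its abstract, the aims for pain and reaction time, and the satisfaction section point to contrasts. A descriptive approach is fully compatible with a difference and its CI.

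**Conclusion.** The point holds in a limited form. For eight outcomes no between-arm estimate is planned. That conflicts with the abstract and does not match the functional hypothesis or the aims for reaction time, pain and satisfaction. The primary comparison, the noninferiority comparison and the spasticity comparisons are unaffected. The conclusion assumes that the 95% CI is meant for each arm, as the sentence reads.

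Two stronger readings are tempting, and the documents support neither.

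- A reader might infer that the comparisons cannot be made at all. An unadjusted difference can be worked out from per-arm means, intervals and numbers, so the accurate statement is that none is planned.
- A reader might infer that arms will be judged by whether their intervals overlap, and that power is lost as a result. Overlap is indeed a stricter rule than the CI of the difference, but no section adopts it. A power loss computed from it would not measure a defect in this plan. The article also gives no effect size or SD for these outcomes other than the FMA.

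**What to change.** In Statistical Methods for Primary and Secondary Outcomes:

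- For each of the eight outcomes, add the toxin-baclofen and toxin-placebo differences with 95% CIs, labelled as estimates without significance claims. One option is a linear model adjusted for center and, where measured, the baseline value, with a method suited to an ordinal scale for the Rankin score. This is not the FMA model in that section, which adjusts for age, center and associated treatment and has no baseline term.
- Restore the 1-month end points for pain and reaction time.
- Analyze satisfaction as values at V1 and V2, not as a change from V0.
- Align the abstract's sentence on regression with this text.

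No new data are needed. Five outcomes at one visit (1-month FMA, Rivermead, Barthel, Rankin, RNLI) and three at two visits (pain, reaction time, satisfaction) give 5 + 3 × 2 = 11 outcome-visit pairs. With two contrasts each, that is 22 estimates, or 26 if sound and visual reaction times are kept apart (13 × 2). They carry no multiplicity adjustment and should be read with caution. In December 2024 the article reported that the database was not yet frozen and no analysis had begun. The change is cleanest if it is fixed before analysis starts.

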#### Methods for Additional Analyses (eg, Subgroup Analyses)

The proportional recovery rule serves as a predictive model for understanding poststroke recovery. It examines the correlation between initial impairment and subsequent recovery by analyzing FMA-UE both at baseline and in follow-up sessions and defines recovery as the change over time [38]. This research suggests that, on average, a significant subset of patients typically regains approximately 70% of their maximum potential recovery from impairment, while a smaller subgroup experiences notably less recovery. For recovery to be considered proportional, patients must recover roughly 70% of their maximum possible potential at the 3-month mark [38]. Patients who initially show mild to moderate deficits according to the FMA-UE (>10) at baseline often follow a pattern known as “recoverers” [39,40]. Those who display a proportional recovery profile tend to have corticospinal tracts that are less affected throughout the entire course [40,41].

Identifying participants with a proportional recovery profile based on the initial FMA-UE seems to be a promising method for participants with stroke, allowing for a more accurate assessment of treatment effectiveness [42]. This subgroup analysis helps to avoid missing treatment effects within the larger group by focusing on those with a “recoverers” profile.

These groups are determined based on whether the FMA-UE is greater than or equal to 11 or strictly less than 11 during the allocation visit [40].

Within the “recoverers” and “nonrecoverers” groups, linear regression models are used in a comparative analysis between the “toxin” and “baclofen” groups regarding the variation in the FMA-UE score. Initially, an unadjusted analysis uses treatment as the sole explanatory variable and the FMA-UE delta score as the response variable. The adjusted model incorporates the patient’s age, the center, and the presence of associated treatment as explanatory variables, in addition to treatment.

The same unadjusted and adjusted models are also computed using the FMA-LE as the response variable in both the “recoverers and the nonrecoverers” groups.

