### Objectives

#### Main Objective

This study aims to demonstrate the superiority of botulinum toxin A over baclofen on motor recovery in the subacute phase after stroke. The primary end point is the change in the Fugl-Meyer Assessment (FMA) motor score from the start of treatment to 3 months later.

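### The recoverer analysis fits toxin v baclofen separately in each subgroup with no interaction term, so it cannot show whether the effect depends on initial FMA-UE; it also leaves part of its own objective without an analysis

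*Protocol article*

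**What the plan says.** The Secondary Objectives include: "To evaluate the impact of treatment on motor recovery (main objective and placebo comparison) based on initial FMA-upper extremity (FMA-UE) scores". The main objective to which this refers is toxin v baclofen, and the Main Objective section gives its endpoint: "The primary end point is the change in the Fugl-Meyer Assessment (FMA) motor score from the start of treatment to 3 months later".

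The matching analysis is under Methods for Additional Analyses. The split is made on a baseline value: "These groups are determined based on whether the FMA-UE is greater than or equal to 11 or strictly less than 11 during the allocation visit". The comparison is then set out: "Within the “recoverers” and “nonrecoverers” groups, linear regression models are used in a comparative analysis between the “toxin” and “baclofen” groups". In the first model, "an unadjusted analysis uses treatment as the sole explanatory variable and the FMA-UE delta score as the response variable". For the second, "The adjusted model incorporates the patient’s age, the center, and the presence of associated treatment as explanatory variables, in addition to treatment". A further response follows: "The same unadjusted and adjusted models are also computed using the FMA-LE as the response variable".

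The section also gives the reason for the analysis: "This subgroup analysis helps to avoid missing treatment effects within the larger group by focusing on those with a “recoverers” profile".

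**The concern.** There are two separate points.

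First, whether an effect depends on initial FMA-UE is a question about the difference between two effects. Two models fitted in two sets of patients give two estimates and two p values, but no estimate or test of that difference. With subgroups of this size, one p value can fall below 0.05 and the other above it by chance when the true effects are equal. The stated aim is to find effects among recoverers that the full comparison would miss. The analysis is therefore an obvious place to look if the primary result is null, and nothing in the section guards against reading a difference in significance as a difference in effect.

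Second, the objective covers more than the method delivers. It names the placebo comparison, and it points to the main objective, whose endpoint is total FMA change. The subgroup method covers toxin v baclofen only, on FMA-UE and FMA-LE only.

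**Working it through.** **Objective and method side by side**

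| | Secondary Objectives | Methods for Additional Analyses |
|---|---|---|
| Comparisons | toxin v baclofen, toxin v placebo | toxin v baclofen |
| Response | total FMA change, by reference to the main objective | FMA-UE change, FMA-LE change |
| Role of initial FMA-UE | effect assessed according to it | separate fits at 11 or above and below 11; no interaction term |

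The general Statistical Methods section supplies none of the missing items.

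**Inputs for the illustration**
- SD 30 and target difference 13, both for total FMA (Sample Size). No SD is given for FMA-UE or FMA-LE, so 13/30 = 0.433 is borrowed as a standardized effect.
- 179 randomized (Results) at 2:2:1 (Allocation): 179 × 2/5 = 71.6, about 72 per active arm. No loss is applied, because FMA, FMA-UE and FMA-LE are to be imputed.
- Two-sided 5%, stated for the primary objective and assumed here.
- Recoverer share not given; 30%, 50% and 70% are assumed.

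**Check of the SD.** The article gives no subgroup power to reproduce, but its noninferiority power can be checked. With 10% loss from 60 and 120, the SE is 30 × √(1/54 + 1/108) = 5.0. Power is Φ(12/5.0 − 1.645) = Φ(0.755) = 77.5%, against 77.6% stated. So 30 is used as the SD.

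**Equal true effect in both subgroups.** With n per arm in a subgroup, power = Φ(13/(30√(2/n)) − 1.96), the opposite tail being negligible.
- n = 36: SE 7.07, ratio 1.838, power 45.2%.
- n = 21.6 (30% of 72): SE 9.13, ratio 1.424, power 29.6%.
- n = 50.4 (70% of 72): SE 5.98, ratio 2.175, power 58.5%.

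The subgroups contain different patients, so the two results are treated as independent. With p1 the power in recoverers and p2 in nonrecoverers, recoverers only is p1(1 − p2) and disagreement is p1(1 − p2) + p2(1 − p1).

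| Recoverer share | p1 | p2 | Disagreement | Recoverers only |
|---|---|---|---|---|
| 30% | 0.296 | 0.585 | 53.5% | 12.3% |
| 50% | 0.452 | 0.452 | 49.5% | 24.8% |
| 70% | 0.585 | 0.296 | 53.5% | 41.2% |

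In all three rows the true effects are identical. A 5% interaction test would declare them different 5% of the time.

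**Power of the interaction test.** Its SE is 30 × √(2/n1 + 2/n2).
- Equal halves: 30 × √(4/36) = 10.0. Power for a 13-point difference is Φ(1.30 − 1.96) plus the small opposite tail, 25.5%. The difference detectable with 80% power is 2.80 × 10.0 = 28.0 points.
- 30/70 split: √(9.13² + 5.98²) = 10.9, power 22.2%, detectable difference 30.6 points.

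**The case against.** The strongest reply is that the objective can be read as asking for the effect within each stratum, which is what the method estimates. The analysis is listed as additional, sets no decision rule, and does not say that p values will be compared across subgroups. An interaction test and reporting rules are often left to the SAP. FMA-UE is a natural response because the proportional recovery rule is defined on it, and both subscores are listed secondary endpoints. The interaction test also has little power.

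Part of this stands. Several stronger readings are tempting but not supported:
- That the plan intends to claim an effect only in recoverers. It says no such thing; the risk lies in the absence of a guard.
- That leaving out placebo and total FMA contributes to that risk. It does not; it is a separate mismatch.
- That the objective names total FMA outright. It reaches it only through the main objective.
- That the split is invalid. It uses a baseline value with a fixed cut-off and is sound.
- That the roughly 50% disagreement is the chance of a false recoverers-only result. It counts both directions; at equal halves the recoverers-only share is about 25%.

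The SAP argument does not remove the point. The article does not leave the subgroup model open. It lists the terms of both versions and gives a purpose that presumes the effect may differ between subgroups. Nor can an SAP settle the mismatch over placebo without departing from either the objective or the method as published. Low power is a reason to call the result exploratory; separate tests do not provide the missing information.

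**Conclusion.** The point holds. As specified, the analysis gives toxin v baclofen effects within recoverers and nonrecoverers but cannot show whether they differ. Under equal true effects, a pattern that looks like a recoverers-only effect would arise in about 12-41% of trials, depending on the recoverer share.

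These figures are illustrative. They rest on an assumed share of 30-70%, on a total-FMA effect size applied to subscore models, on about 72 per active arm, and on a normal approximation. The lack of an interaction term does not depend on them.

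Separately, the toxin v placebo comparison by initial FMA-UE is an explicit objective with no described analysis, and total FMA change by subgroup is an implied one. Both points concern a secondary objective and leave the primary analysis untouched. They should be corrected before analysis.

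**What to change.** For each response, fit one model with treatment, subgroup (FMA-UE 11 or above v below 11), treatment × subgroup, and the existing covariates: age, center and associated treatment. The unadjusted version keeps the first three terms. Report the interaction and both subgroup effects with 95% CIs from that model, label them exploratory, and state that no claim of a differential effect will rest on subgroup p values alone.

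Then reconcile the objective with the method: either add toxin v placebo and total FMA change by subgroup, or narrow the objective to what is analyzed. If the placebo comparison is added, its imprecision should be stated. With about 36 on placebo (179/5 = 35.8) and equal halves, the SE for total FMA is 30 × √(1/36 + 1/18) = 8.7, so the 95% CI half-width is 1.96 × 8.7, about 17 points, wider than the 13-point noninferiority margin.

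The cost is wording and some programming, with no new data. The article reports that no statistical analysis had been done as of December 2024. The drawbacks are the low interaction power shown above and the assumption, in a joint model, that covariate effects are common to both subgroups.
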